#### Exclusion criteria

Exclusion Criteria will include: ongoing rheumatic or inflammatory joint diseases other than RA; serious medical diseases such as: hyperlipidemia, hyperglycemia, diabetes mellitus, cardiovascular diseases, gastrointestinal disease, liver disease or renal failure; patients with RA who have a prominent component of comorbid fibromyalgia syndrome, prior treatment with TwHF agents, glucocorticoids, or biological agents; skin allergies or broken skin in the areas of planned treatment with topical TwHF gel. Female patients who are pregnant, breast-feeding or who plan to become pregnant will be excluded.

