Tripterygium wilfordii Hook F (TwHF), a traditional Chinese herb, has been used to relieve joint pain for a thousand years in China and its extracts have recently proven to be effective in patents with RA [2, 3]. However, the oral application of TwHF is limited for clinical use because of its high frequency of reproductive system damage [4]. In order to reduce toxicity without losing efficacy, the current study utilizes a topical rather than an oral compound THwF, hoping to thereby explore the advantages of CET. We previously conducted a 4-week double-blinded, randomized, placebo-controlled pilot clinical trial on topical compound TwHF with 70 RA patients whose joint disease was severely-active. The findings of the pilot study showed that joints pain and swelling were rapidly (within one week) reduced with the application of topical compound TwHF twice a day. Furthermore, a favorable control of the overall RA disease condition was found, as the rate of achievement rose to 20% and 50% improvement in the (ACR20 and ACR50) were 34% and 17% at week 4, using intention to treat analysis [currently awaiting publication]. The ACR20 and ACR50 response rates were found to be even higher in another study which reported responses of 58% and 20% with the TwHF group at week 6 [5]. Additionally, a previous double-blind, randomized multicenter trial found that based upon methotrexate or leflunomide, 75 out of 87 patients (90.8%) in the topical compound TwHF group and 58 out of 87 patients (69.0%) in the topical placebo-treated group reported relief from their joint pain [6].

Encouraged by the above results, we have developed the topical compound TwHF to be used as a hospital gel preparation. Thus, we plan to undertake an 8-week double-blinded randomized placebo-controlled clinical trial to further explore the safety and effectiveness of topical TwHF gel in patients with active RA.

It is important to examine whether topical treatment, with TwHF gel, as a supplement to usual care, will result in better outcomes for patients with active RA. We expect a favorable outcome for the topical compound TwHF gel that supports its efficiency. This article provides a full description of the study’s design and methodology in accordance with the SPIRIT guidelines for reporting protocols for intervention trials and the CONSORT guidelines [7, 8] for reporting outcomes.

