### Participants

#### Inclusion criteria

Eligible patients, men and women, must age from 18 to 65 years old, and must be clinically diagnosed with RA prior to screening for study entry in accordance with the 1987 revised criteria of the American College of Rheumatology [9]. Their RA disease stage must be in the moderate activity range, as defined by the criteria of the 28-joint count Disease Activity Score (DAS-28 score), ranging between 3.2 to 5.1 [10]. If patients are receiving a disease-modifying, anti-rheumatic drugs (DMARDs), those medications should be continued unchanged throughout this study, but their dosages must have been stable for at least 12 weeks prior to study entry.

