The safety evaluation will be accomplished by a face-to-face interview at the 4th and 8th weeks and by a a telephone-interview with the remote 12th week follow-up. Adverse experiences of interest will include: manifestations of cutaneous allergy (erythema, edema, itching) and gastrointestinal stimulation due to mucous membrane damage. In addition, because of the high frequency of reproductive system damage, the safety evaluation will focus on changes in menstruation patterns among premenopausal female participants. The relevant female participants will be asked a general question about whether they have observed any change in their menstruation pattern. Irrespective of how they answer that question, a series of follow-up questions will attempt to quantify any change in the menstrual cycle (extension, shortening or no change), or in the quantity of menstrual flow (increased, reduced, or unchanged). Blood and urine routine laboratory examinations, including glutamic-pyruvic transaminase, glutamic oxalacetic transaminase, creatinine and urea nitrogen will be accomplished at baseline and on the 8th week. Quantitative changes will be addressed on the record. Professional judgments regarding the severity of any given adverse effect and any recognized relationship between the adverse effect and the study interventions will be documented if any of the above safety measures are observed to fall beyond normal clinical or laboratory ranges.

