## Discussion

To date, only a small number of studies have documented the effectiveness of CET using any pharmacological agent. This clinical trial is designed as a double-blinded, randomized, controlled study of TwHF-based CET in a moderate active RA population with 8 weeks of observation. Considering the main clinical features of active RA to be joint swelling, tenderness, and pain, these are the clinical manifestations monitored using validated instruments. It is anticipated that topical compound TwHF gel will also be effective in controlling the clinical manifestations of RA and safe for use by RA patients.

In animal studies, TwHF microemulsion has been observed to imeliorate the severity of a murine adjuvant-induced arthritis model and to reduce the male reproductive toxicity and hepatotoxicity [14]. It is hoped that the topical use of TwHF as a clinical application of CET in RA patients will be found to be both safe and efficacious. Although TwHF and its extracts have shown good responses in patients with RA it is currently limited to use in elderly patients because of demonstrated reproductive toxicity. Safety observations from previous studies have shown that compound TwHF applied topically can cause cutaneous reactions which are reversible with discontinuation of the topical TwHF compound. In addition, increases in serum aminotransferase and alterations in menstruation among female patients have been reported [5, 6].

There are several aspects of the current study design that are different from previous CET clinical studies using this agent. Firstly, the design of dosage adjustment in this study will demonstrate whether the period of dosage reduction will bring additional benefits to the patients. In clinical practice, patients often continue to apply the effective medicine for an additional period in order to consolidate the efficacy, though there is no evidence to support this practice. Secondly, the follow-up assessment has rarely been included in CET research. Since oral preparations of THwF have often exhibited side effects, such as gastrointestinal and menstrual disorders, special emphasis has been placed upon an 4-week follow-up (to monitor at least one menstrual cycle).

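### Reproductive toxicity is the named hazard of TwHF for both sexes and men from 18 are eligible, but the printed parenthood exclusion and targeted reproductive questions cover women only

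*Protocol article*

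**What the plan says.** **Hazard.** The Background of the protocol article states that "the oral application of TwHF is limited for clinical use because of its high frequency of reproductive system damage". The Discussion says of TwHF and its extracts that "it is currently limited to use in elderly patients because of demonstrated reproductive toxicity". Neither sentence names a sex. The Discussion also describes an animal arthritis study in which a TwHF microemulsion was seen to "reduce the male reproductive toxicity and hepatotoxicity". For earlier studies of the topical compound, it notes that "alterations in menstruation among female patients have been reported".

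**Who can enter.** Inclusion criteria: "Eligible patients, men and women, must age from 18 to 65 years old".

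**Who is kept out on reproductive grounds.** Exclusion criteria: "Female patients who are pregnant, breast-feeding or who plan to become pregnant will be excluded". No corresponding line for men is printed.

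**What is asked.** The safety paragraph under Outcome measurements says that "because of the high frequency of reproductive system damage, the safety evaluation will focus on changes in menstruation patterns among premenopausal female participants". It then sets out questions on cycle length and menstrual flow. The interviews are face to face at weeks 4 and 8 and by telephone at week 12. The abstract says that safety evaluation at these three times rests on spontaneous complaints from the study subjects, with special emphasis on skin allergy and menstrual change. The laboratory tests listed are routine blood and urine with liver and kidney measures, at baseline and week 8.

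**The concern.** The precautions are narrower than the hazard that the article itself describes. Reproductive damage is the toxicity it names when explaining why oral use is limited and why a topical route was chosen. It says that TwHF is kept to older patients for this reason, yet the trial admits adults of both sexes from age 18. Women receive an entry rule and a set of prompted questions; men receive neither in print.

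What is at stake is patient protection. If staff follow the text as written, a man who intends to father a child during the trial can be enrolled. A reproductive symptom in a man, or a pregnancy in his partner, would be recorded only if he raised it himself. The comparison of ACR20 response between groups is not touched.

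**Working it through.** No arithmetic applies: the point does not depend on the sample size, the power or a rate. The check sets the relevant sections side by side.

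| Question | Women | Men | Section |
|---|---|---|---|
| Eligible at 18 to 65 years? | Yes | Yes | Inclusion criteria |
| Covered by the general wording of the hazard? | Yes | Yes, no sex is named | Background; Outcome measurements; Discussion |
| Sex-specific evidence mentioned? | Menstrual changes in patients | Male reproductive toxicity in an animal study, reduced by a microemulsion | Discussion |
| Excluded if planning a child? | Yes | No rule printed | Exclusion criteria |
| Targeted reproductive questions? | Yes, if premenopausal | None printed | Outcome measurements |
| Laboratory measure of reproductive function? | None named | None named | Outcome measurements |
| Can report complaints at weeks 4, 8 and 12? | Yes | Yes | Abstract (Methods); Outcome measurements |

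1. **The hazard is not limited to women.** The general statements name no sex. The animal sentence shows that the authors recognise a male form of the toxicity, since a preparation can only reduce a toxicity that is otherwise there.

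2. **Men of reproductive age are eligible.** The inclusion criterion names men explicitly and starts at 18.

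3. **The printed safeguards stop at women.** The exclusion sentence opens with female patients. The safety paragraph gives reproductive damage in general as its reason and then turns at once to menstruation, which cannot detect anything in a man.

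4. **Men are not left without any route.** The interviews are not restricted by sex, and spontaneous complaints are open to everyone. The gap is the absence of a printed entry rule and of a prompted question.

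5. **Size.** The article gives no expected share of men among the 168 patients and no male event rate for oral or topical TwHF. The risk therefore cannot be quantified from the documents, and an invented share of men would add nothing to the case for the change.

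**The case against.** The strongest reply is that this is a condensed article. The exclusion list is introduced as what the criteria will include, which need not be exhaustive, and the full protocol could hold a rule on contraception or fathering as well as the complete interview form. It can also be argued that focusing the questions on menstruation is sensible, because that is the human signal reported with the topical compound. The high frequency of damage stated in the Background concerns oral use, and the male evidence is one animal sentence in which toxicity went down.

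Much of this stands, and it keeps the point minor. It does not remove it. The article does more than stay silent on reproductive precautions: it prints a specific rule and a specific question set, and both are narrower than the hazard given as their reason. If the full protocol already has a male rule, printing it settles the entry part.

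A reader might infer three stronger things that the documents do not support:

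- **That the gel harms men.** No human data on male reproductive effects are given, and the only male evidence comes from animals.
- **That men's safety is not monitored.** They are interviewed at weeks 4, 8 and 12, may report any complaint, and have the same laboratory tests.
- **That the trial will claim reproductive safety for both sexes on data from women.** No section plans such a conclusion. The expectation that the gel will be effective "and safe for use by RA patients" concerns overall safety.

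**Conclusion.** The point holds as a minor, precautionary safety gap. The article describes reproductive toxicity without a sex limit and enrols men from 18, but directs its printed parenthood exclusion and its targeted reproductive questions to women only. It rests on two assumptions: that the printed criteria and interview content are what staff will follow, and that the animal finding together with the general wording of the hazard is enough to justify an inexpensive precaution. The size of the risk to men is unknown. The primary outcome, the secondary outcomes, the 84 patients per group and the planned tests all stay as they are. Confidence is medium, because the full protocol is not shown.

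**What to change.** 1. **Exclusion criteria.** Add men who plan to father a child during weeks 0 to 12, that is, the 8 weeks of treatment plus the 4 weeks of follow-up. If the full protocol already contains such a rule, print it.

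2. **Safety evaluation under Outcome measurements.** Add one question for men on reproductive symptoms and partner pregnancy to the existing interviews at weeks 4, 8 and 12. This also picks up unplanned pregnancies, which an entry rule cannot prevent.

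The cost is one eligibility line and one interview item at three contacts already planned, with no extra visit or laboratory test. The downside is that a few men will not be enrolled. A single question cannot establish male fertility safety, and pregnancies that become known after week 12 would not be captured.

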### Randomization

Randomization will be controlled by an independent third party, the hospital Clinical Evaluation Center, using the SAS system (Version 8.2 for Windows) to assign the eligible participants at a 1:1 ratio to receive either topical compound TwHF gel or placebo.

### Blinding

This study is a double-blind and placebo-controlled design. The blinding will also be accomplished and monitored by the hospital Clinical Evaluation Center. The blinding codes record topical compound TwHF gel and the placebo as A and B, sequentially and the details of the allocation sequence will be put in sealed light-tight envelopes and maintained in the Clinical Evaluation Center. The contents of these envelopes will be unknown to the principal investigator, the study staff, and the participants. Since the packing and labeling of the treatment gels are the same, the topical compound TwHF gel and placebo gel will be masked by numeric codes from 001 to 168, which correspond with each participant’s sequential enrollment number. Thus, the study researchers will enroll and evaluate study subjects but will have no influence on randomization. So the case group division is adapted to a randomized, double-blind study design.

### Intervention

The ingredients for the compounding of the topical TwHF gel include: Tripterygium wilfordii Hook F, Mangxiao (Mirabilite), Chuanxiong (Rhizoma Ligustici), Ruling (Olibanum), and Moyao (M yrrh) (proportions: 4:4:2:2:1). The topical placebo gel is made of a viscous agent and sucrose which make it looks like the active preparation. Both of the gels will be prepared by the Pharmaceutical Department of Guang’anmen Hospital, and the herbs will be purchased from Beijing Fengtaijinyuan Pharmaceutical Co., Ltd. Each gel is 20 gram (g) per tube. Both the topical compound TwHF gel and the placebo gel will be applied for 1st to 5th metacarpophalangeal joints, 1st to 5th proximal interphalangeal joints, wrists, knees and ankles 10 g for 1 h, once a day from week 0 through week 4 and 10 g from week 5 through week 8.

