## Methods

### Study design

This clinical trail will be accomplished at Guang’anmen hospital, China academy of Chinese Medical Science in Beijing, China. The current study follows the guidelines of the Declaration of Helsinki for humans and has been approved by the ethic s committee of Guang’anmen Hospital (approval number: 2016–062-KY). Enrolled will be 168 patients with documented moderately active RA who will be randomized (1:1 ratio) to one of two treatment groups: the TwHF gel group and the placebo gel group. Written signed consent will be obtained from each participant before any study-related procedures are initiated.

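### The gel amount is the same in weeks 0–4 and 5–8, yet the Discussion relies on a dosage reduction, and a two-arm trial with one shared schedule cannot show what a reduction adds

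*Protocol article*

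**What the plan says.** The Intervention section divides treatment into two periods and gives the schedule in one phrase: "10 g for 1 h, once a day from week 0 through week 4 and 10 g from week 5 through week 8". The schedule is common to the arms: "Both the topical compound TwHF gel and the placebo gel will be applied for" the same list of joints.

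Under Study design, patients go to "one of two treatment groups: the TwHF gel group and the placebo gel group". Under Randomization, they are assigned "at a 1:1 ratio to receive either topical compound TwHF gel or placebo". No second randomisation is described.

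The Discussion lists features that set this trial apart from earlier studies of the agent. The first is that "the design of dosage adjustment in this study will demonstrate whether the period of dosage reduction will bring additional benefits to the patients". The reason offered is that in practice "patients often continue to apply the effective medicine for an additional period in order to consolidate the efficacy".

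The Data analysis section plans between-group tests of ACR20 and ACR50 at weeks 4 and 8. For DAS28 it plans between-group t tests and paired t tests from baseline to after treatment within each group.

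**The concern.** There are two linked problems.

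- **The regimen.** The sentence on gel use breaks the course after week 4 but prints the same amount on both sides of the break. A reader of the Intervention section finds no reduction, while a reader of the Discussion is told that there is one. If the text is followed as printed, the regimen for weeks 5–8 is either unchanged or not fully defined. The primary endpoint, ACR20 at week 8, is measured at the end of that period. What is at stake is whether the tested intervention can be described and reproduced, and whether adherence and safety findings can be tied to a known exposure.
- **The inference.** The Discussion promises a conclusion about the reduction period. That needs a comparison between patients who had the reduction and similar patients who did not. If the trial has no such comparison, the promise invites a later reader to take a change from week 4 to week 8 as evidence about dosing.

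**Working it through.** No sample-size or power figure bears on this point. The check sets the passages side by side and then asks which contrasts the design can estimate.

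**Step 1: is a reduction specified?** Inputs from the Intervention section:

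| Period | Amount | Application time | Frequency |
|---|---|---|---|
| Weeks 0–4 | 10 g | 1 h | once a day |
| Weeks 5–8 | 10 g | not stated | not stated |

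Ratio of amounts, second period to first: 10 g / 10 g = 1.0.

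The sentence can be read in two ways.

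- *The time and frequency carry over to the second period.* The weekly amount is then 10 g × 7 = 70 g in both periods. Exposure is identical, and the reduction described in the Discussion does not exist.
- *They do not carry over.* A reduction could then lie in frequency or application time, but neither is stated. The Discussion relies on something the document never defines.

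A misprinted amount or a dropped frequency would each explain the text. The document does not say which, and this review does not choose between them.

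**Step 2: could the design show what a reduction adds, once it is properly stated?** The inputs are two arms, a single 1:1 allocation, and one schedule for both gels. The claimed benefit can mean two things:

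| Meaning of the claim | Comparator needed | Patients randomised to it |
|---|---|---|
| Reducing compared with not reducing | An arm kept on the first-period schedule | 0 |
| Continuing at a reduced level compared with stopping | An arm that stops at week 4 | 0 |

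**Step 3: what do the available contrasts estimate?**

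- *TwHF minus placebo at week 8:* the effect of the whole 8-week schedule.
- *TwHF minus placebo at week 4:* the effect of the first period.
- *The difference between those two:* how the effect over placebo evolves under one fixed schedule. It does not separate a reduction from longer treatment.
- *Week 4 to week 8 change within the TwHF arm:* a mixture of any reduction, longer exposure and the passage of time. It has no randomised reference for the reduction.
- *Paired baseline-to-posttreatment tests:* change from the start of treatment, which says nothing about the switch after week 4.

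None of these isolates the reduction, and the Data analysis section plans no test that sets week 4 against week 8.

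**The case against.** The strongest reply is that the trial's real question is not affected. The objectives, the primary outcome and the sample size all concern TwHF gel against placebo. Both arms share a schedule, so an unclear description does not by itself bias that comparison. **This stands.**

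A second reply is that the article condenses a fuller document. The trial runs at one hospital under audited standard operating procedures, and these may state the week 5–8 frequency and application time. **This stands in part.** A missing frequency alone would not be a finding, and it is not shown that any patient would be wrongly treated. But the point is a conflict between two printed statements, not an omission, and an unseen procedure does not remove it.

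A third reply is that the between-group comparisons at weeks 4 and 8 do show whether benefit over placebo persists through the second period, which is close to the stated interest in consolidating efficacy. **This too stands in part.** Persistence under one schedule is worth reporting, but it does not tell reducing from not reducing, or continuing from stopping. The Discussion claims more than persistence.

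Finally, drop-out could be called a distraction here, since no week 4 to week 8 analysis is planned for it to confound. **That is fair**, and the conclusion does not depend on it.

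**Conclusion.** The concern holds in both parts.

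- The Intervention section and the Discussion contradict each other on whether dosage changes after week 4. This leaves the regimen unsettled for 4 of 8 treatment weeks, and the shared schedule applies to all 168 patients. These are patients under an unclear description, not patients shown to have been treated wrongly.
- The Discussion's claim about the reduction period has no support in the design, because no patient is randomised to an alternative week 5–8 schedule. This stays true however the dosing text is corrected.

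The week-8 comparison of TwHF gel with placebo remains valid for whatever schedule is applied, provided that both arms follow it. The conclusion assumes only that the article reports the arms, the allocation and the shared schedule correctly. The contradiction should be resolved before the trial is conducted or reported from this text. On its own, the overclaim would need only a change of wording.

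**What to change.** 1. Reconcile the Intervention section with the Discussion so that amount, frequency and application time are stated for each period and agree in both places. The sponsor must say which text reflects the intended regimen; no regimen is suggested here.
2. Replace the Discussion's claim about the reduction period with a statement that the trial compares TwHF gel with placebo over the whole 8-week schedule.
3. State that any week 4 to week 8 change, within an arm or in the difference between arms, is descriptive and does not estimate the effect of a dosage change.

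The cost is a protocol clarification and a narrower claim. No arm, patient, visit or test is added.
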